#### Secondary outcome measures

The secondary outcome measure at GP level is GP’s attention for the patients’ work related problems as it is perceived by patients. It is measured by a self-constructed five item scale, with 2 response categories: “yes” or “no” concerning: 1. Does the GP know your occupation? 2. Do you think the problem for which you consulted the GP is work related? 3. Was this possible relationship discussed by your GP? 4. Did your GP discuss sick leave? 5. Did the GP help you to find solutions for work-related problems?

As mentioned above, intervention group GPs are asked to fill in a form for each participating patient with questions on the same topics. This will provide us with information about the extent to which intervention group GPs and patients agree on these issues.

Secondary outcome measures at patient level consist of productivity, sick leave duration, health related to work, quality of life, self-rated health and direct illness-related costs, health care and non-health care. Measures for productivity are both absenteeism and presenteeism. Absenteeism refers to the total days lost from work. Presenteeism refers to attending work whilst still sick or disabled, causing reduced productivity while at work [22,24,25]. Sick leave and presenteeism will be measured with modules C and D of the Productivity and Disease Questionnaire (Prodisq) [26]. The Prodisq is developed based on the Quantity and Quality (QQ) method and provides a reliable and valid tool for measuring quantity and quality of work on a daily basis [25,26]. Quality of life will be measured by means of the RAND-36 and EQ-5D-5 L [27,28]. The RAND-36 consists of 8 subscales: physical functioning, role limitations due to physical problems, social functioning, bodily pain, general mental health, role limitations due to emotional problems, vitality, and general health perceptions [28]. The EQ-5D-5 L is an improved version of the Euroqol (EQ-5D). In contrast to the Euroqol, the EQ-5D-5 L has 5 levels of severity in 5 dimensions, instead of 3 levels of severity in 5 dimensions, which improves the instrument’s sensitivity [28].

Self-rated health will be assessed using one item from the Short Form Health Survey (SF-36). This widely used measurement tool describes how a respondent values and assesses his/her general health [29]. To detect health complaints and co-morbidity underlying work disability, questions derived from The Netherlands Working Conditions Survey (NWCS) will be used [30].

Direct costs, both healthcare and non-healthcare, will be measured by an adapted version of the Trimbos/iMTA questionnaire (TiC-P) [31].

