#### Patients

The patient population will exist of patients (from the lists of the participating GPs) who are 18–63 years of age, have paid work (paid-employment or self-employed) for at least 12 hours per week and have sufficient understanding of the Dutch language to fill in a questionnaire. The upper age limit of 63 was chosen to lower the chance that patients drop out during follow-up due to retirement.

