### Procedures

Inclusion will take place during a 4 month period, starting after the training of the intervention group GPs. The GPs’ receptionists will approach patients in the waiting room with a short questionnaire about age, number of working hours and their willingness to participate in the project. If a patient meets the selection criteria and signs informed consent the patient will be included and receive the first questionnaire. A second and third questionnaire will follow after 6 and 12 months. Forty patients for each participating GP, 20 females and 20 males, will be included for the study.

Only the intervention group GPs will be asked to fill in a form for each consenting patient with questions about: 1 the occupation of the patient; 2 the work relatedness of the problem that he/she presented; 3 whether sick leave was discussed; 4 whether the GP had suggested contacting an OP; 5 whether the GP had stimulated the patient to adopt a pro-active coping style. Two final questions asked whether the GP thought the training had been helpful for the consultation and if the GP had enough time for the consultation.

The control group will deliver care as usual. As it could be surmised that their usual care is influenced by the data collection we try to make sure that the data collection in the control group practices is carried out as much as possible by the receptionists supported by a research assistant. When data collection is completed the control group GPs are offered the same training as the intervention group as an incentive for adherence to the study protocol.

Patients will be approached by the receptionist before the consultation and, if they are prepared to participate in the study, are asked to answer the first questionnaire after the consultation and a second and third questionnaire after six and twelve months respectively.

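### The five-item scale for perceived GP attention counts the patient's own view of whether the complaint is work related, and offers only yes or no for items that do not apply to every patient

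*Protocol article*

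**What the plan says.** In the Protocol article, under Secondary outcome measures, the single secondary outcome at GP level is the GP's "attention for the patients’ work related problems as it is perceived by patients". The instrument follows: "It is measured by a self-constructed five item scale, with 2 response categories", namely yes and no. Its items are:

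- Item 1: whether the GP knows the patient's occupation.
- Item 2: "Do you think the problem for which you consulted the GP is work related".
- Item 3: "Was this possible relationship discussed by your GP".
- Item 4: "Did your GP discuss sick leave".
- Item 5: "Did the GP help you to find solutions for work-related problems".

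The same section adds that intervention GPs complete a form on the same topics, so that agreement between GP and patient can be studied.

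Under Patients, eligibility rests on age, sufficient Dutch, and that patients "have paid work (paid-employment or self-employed) for at least 12 hours per week". A work-related complaint is not required. Under Procedures, "Inclusion will take place during a 4 month period, starting after the training of the intervention group GPs", and patients answer the first questionnaire after the consultation. The article does not say how the five answers are combined.

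**The concern.** A scale of GP attention should move when GPs behave differently and stay put when they do not. Item 2 fails this test on its face. A patient who believes the back pain comes from the job answers yes whether or not the GP mentions work.

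Items 3 and 5 do concern the GP, but they presuppose a possible or actual link with work. A patient who sees no such link has no answer that says the question does not apply, and a no from that patient cannot be told apart from a no that reports inattention.

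This is the only GP-level secondary outcome. It is also the only measure in both arms of what GPs do in the consultation: the GP form is completed in the intervention arm only, and the GP-level primary outcomes concern registration in the medical record. If the score moves with the kind of complaint patients bring, a real change in GP behaviour is diluted, and a difference between arms is harder to read.

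**Working it through.** **Planned figures.** The article gives no expected rates for this scale, so there is no planned figure to reproduce for it. The only sample-size figure is for the return-to-work self-efficacy scale. It reproduces: 63 patients per arm for a difference of 0.57 with SD 1.14, times a design effect of 1 + 29 × 0.15 = 5.35, gives 337.05; divided by 30 this is 11.2, rounded up to 12 GPs per arm. It has no bearing on this point.

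**The items set against the construct.**

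| Item | Describes GP behaviour? | Applies to every eligible patient? |
|---|---|---|
| 1 Occupation known | Yes | Yes, all have paid work |
| 2 Problem work related | No, patient's opinion | Yes |
| 3 Possible link discussed | Yes | Not clearly; refers back to item 2 |
| 4 Sick leave discussed | Yes | Can be answered by all; need depends on the complaint |
| 5 Help with solutions | Yes | No; presupposes a work-related problem |

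**Illustration.** All rates below are assumptions, as is the simple sum of yes answers. Let w be the share answering yes to item 2. Let item 1 be yes in 60% of patients, and items 3, 4 and 5 be yes in 50%, 30% and 40% of patients with a work-related complaint and no otherwise. GP behaviour is held identical throughout.

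- All five items: 0.60 + w + w × (0.50 + 0.30 + 0.40) = 0.60 + 2.2w
- Without item 2: 0.60 + 1.2w

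| w | Five items | Without item 2 |
|---|---|---|
| 10% | 0.82 | 0.72 |
| 20% | 1.04 | 0.84 |
| 30% | 1.26 | 0.96 |
| 40% | 1.48 | 1.08 |
| 50% | 1.70 | 1.20 |

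A 10-point difference in w (20% against 30%) shifts the five-item score by 1.26 − 1.04 = 0.22, of which 0.10 comes through item 2 and 0.10 × 1.2 = 0.12 through items 3 to 5. The shift is proportional to the imbalance: 0.05 × 2.2 = 0.11 for 5 points and 0.20 × 2.2 = 0.44 for 20 points.

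A second set of assumptions (30% against 40%, items 3 and 5 yes in half of work-related cases, items 1 and 4 unrelated to the complaint) gives 0.10 + 2 × 0.5 × 0.10 = 0.20.

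**Relaxing the strictest assumption.** If patients without a work-related complaint also answer yes to item 3 at some rate r, that item contributes 0.10 × (0.50 − r) rather than 0.05. The same holds for items 4 and 5. If the rates were equal in the two kinds of patient, only the 0.10 from item 2 would remain. The item 2 part does not depend on the assumed rates; the remainder does.

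**Comparison with a real effect.** With w at 30% in both arms, raising each of items 3 to 5 by 10 points among work-related complaints shifts the score by 0.30 × (0.10 + 0.10 + 0.10) = 0.09. On these assumptions a 10-point case-mix difference outweighs it.

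**The case against.** The case against has four parts.

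*No scoring rule is stated.* A reader might infer that inapplicable items are scored as no, or that the five answers are summed with equal weight. The article says neither. A blank, or item 2 used only as a lead-in, is not excluded, and a condensed article may leave scoring to a fuller document. This stands: the absence of a scoring rule is not the point made here. What is printed is that item 2 is one of the five items of the scale that measures GP attention, and that only two answers are offered.

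*Item 2 has other uses.* It introduces item 3 and is the patient's side of the GP-patient agreement comparison. This also stands. It is a reason to keep the question, not to count it as GP attention.

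*Items 3 and 5 are not closed to patients who see no link.* A reader might infer that such patients must answer no to both. That is too strong. Item 3 concerns a possible relationship, which a proactive GP may raise unprompted, and the Background describes a two-way relation between work and health, so a complaint that work did not cause can still create problems at work. Only item 2 is fixed by the patient's opinion.

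*Randomisation of practices balances case mix in expectation.* Receptionists approach patients before the consultation, on criteria unrelated to the complaint. This stands as to the default: the effect is mainly noise and dilution. It is not a full answer, because patients are included after the training, and because item 2 is answered after a consultation in which a trained GP may have changed the patient's view.

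**Conclusion.** The point holds in limited form. Item 2 does not measure the stated construct, and the response format of items 3 and 5 does not fit every eligible patient. A score built from all five items would mix case mix and patient belief with GP behaviour. It would be biased, rather than merely noisier, only if recruitment after allocation differed by arm or the training altered answers to item 2. The article does not show that either happens.

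Under a simple sum, item 2 alone contributes 0.10 points for each 10-point difference in the share of work-related complaints, and the total moves by about 0.2 of 5 on the assumed rates. These figures should not be read as an expected bias in the trial: the sum score, the rates and the 10-point imbalance are all assumptions.

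The matter concerns one secondary outcome. The change is still worth making, because it is cheap and brings the only GP-level secondary outcome closer to what it is said to measure.

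**What to change.** - Keep item 2 in the questionnaire but out of the GP-attention score. Report it separately by arm and use it for the GP-patient agreement comparison.
- Add a 'not applicable' option to items 3 and 5, and report how often it is chosen in each arm.
- Compare items 1, 3, 4 and 5 between arms in all patients with the planned multilevel model.
- Do not restrict items 3 to 5 to patients who answer yes to item 2. That answer comes after the consultation and may itself be affected by the training, and the restriction would discard consultations in which the GP discussed a link that the patient does not accept.
- Do not ask about work-relatedness in the waiting room. It could prompt patients in both arms to raise work, and Procedures already voices concern that data collection may influence usual care in the control practices.

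The cost is a score with one item fewer and a small rewording of a self-constructed form, so no validated instrument is altered. The change does not remove all dependence on case mix: in the illustration above, leaving out item 2 alone reduces the shift from 0.22 to 0.12. The 'not applicable' counts make the remainder visible.

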### Process evaluation

A short questionnaire and individual interviews will be used to examine whether there are any identifiable facilitating factors and perceived barriers for implementation of our education programme.

### Cost-effectiveness evaluation

The cost-effectiveness of the intervention will be evaluated from the perspective of society at large whereby the costs and benefits will be captured independently of those who bear the costs and those who receive the benefits. We will measure and value health care costs and non health care costs, like productivity costs and costs related to the intervention. Health care costs include costs directly related to the provision of health care, such as costs for primary and secondary care, but also costs for drugs and alternative treatments. These costs will be calculated following the cost calculation guidelines for health care in the Netherlands [32]. The prices of prescribed drugs will be based on Daily Defined Dosage (DDD) taken from the Royal Dutch Society for Pharmacy [32]. The direct non-health care costs are calculated using the information obtained from the cost questionnaires and shadow prices. Productivity costs are costs in paid labour as a consequence of sickness, sick leave and disability of a productive person. The most important productivity costs will be measured in terms of lost productivity: presenteeism, absenteeism and compensation mechanisms. Lost productivity will be calculated by using the friction cost method which basically multiplies the days of production loss until replacement by the average day wage [32]. For the latter method, the Dutch guideline for economic evaluation is used [32]. The costs directly related to the development and implementation of the intervention will be registered. Detailed information concerning the methods of economic evaluation can be found in the article by Noben et al. [33].

### Statistical analysis

#### Sample size

The sample size calculation was based on the outcomes of the RTW-SE in a reference group consisting of employees who were sick listed for more than 13 weeks. Here the mean score was 4.24 with a standard deviation of 1.14. We want our study to allow us to demonstrate a moderate effect of our intervention. Cohen defined a moderate effect as a difference of a half standard deviation [34]. Therefore we need two groups of at least 12 GPs, based on a power of 80% and an alpha of 0,05. Assuming a loss of 25%, they have to recruit 40 patients each to be able to analyse 30 patients. This calculation is based on a conservative estimate of the intra cluster correlation coefficient of 0.15.

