## Methods

### Trial design

The study is a cluster randomised controlled trial using randomisation on practice level to prevent contamination. We will randomise the practices into two groups with a 1:1 allocation ratio. GPs in the intervention group practices will receive the training program, GPs in the control practices will deliver care as usual.

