### Randomisation

We aim to recruit at least 24 GPs who will be randomised into an intervention group and a control group. To prevent contamination, we will randomise clusters on practice level. A statistician will generate a block randomisation scheme using a block size of 2 and practices will be assigned to either condition according to the order in which they are recruited. After this order is established the allocation of the random sequence will be performed by the researcher.

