#### Effect evaluation

The outcomes of the questionnaires will be compared between both groups at the three different measurements. Descriptive statistics will be used to summarise the data and detect outliers, missing values and data entry mistakes. We will describe the categorical variables using frequency tables; for each continuous variable we will calculate minimum, maximum, range, median, mean and standard deviation. The data will be further analysed using a multi level model to assess the influence of the different variables. All analyses will be performed at patient level according to the intention to treat principle, so patients will be regarded as belonging to the intervention group if their GP was allocated to the intervention condition, regardless of whether the GP effectively received the training.

The primary independent variable in the analyses will be the GPs’ exposure to the training: trained GP or control group delivering usual care. The primary dependent variables are their patients’ score on the RTW-SE scale, the number of Z05 codes used by the GPs and the proportion of working age patients for whom the occupation is registered. Effects of the intervention will be checked for effect modification by experience and gender of the GPs. All analyses will be performed with SPSS. Effects on the different outcome variables will be assessed at a significance level of 0.05.

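### The sample size treats each GP as an independent cluster although practices are randomised, so the stated 80% power depends on few multi-GP practices or negligible correlation between GPs of one practice

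*Protocol article*

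**What the plan says.** The Trial design section of the protocol article makes the practice the unit of allocation: "We will randomise the practices into two groups with a 1:1 allocation ratio". The Randomisation section repeats this and gives the reason: "To prevent contamination, we will randomise clusters on practice level". The same section states its recruitment target in GPs: "We aim to recruit at least 24 GPs who will be randomised into an intervention group and a control group".

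The Sample size section is also in GPs: "Therefore we need two groups of at least 12 GPs, based on a power of 80% and an alpha of 0,05". Its inputs concern the return-to-work self-efficacy scale (RTW-SE), the patient-level primary outcome. They are a reference population ("Here the mean score was 4.24 with a standard deviation of 1.14"), a target difference of half a standard deviation, 40 patients recruited and 30 analysed per GP, and an ICC of 0.15, which the authors call conservative.

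The article does not say how many practices are expected, how many GPs a practice may supply, or whether the 0.15 applies to GPs or to practices.

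**The concern.** In a cluster-randomised trial, power is governed by the number of randomised units and by the correlation among all patients within one unit. Here that unit is the practice. If a practice supplies two GPs, all their patients are in the same arm, and the cluster has 60 analysed patients instead of 30. With 24 GPs in total, there are then fewer and larger clusters than the calculation assumes.

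Several GPs from one practice is a realistic case. Randomising practices to prevent contamination serves its purpose mainly when colleagues in one practice may both take part. The Participants section invites GPs as individuals and sets no limit per practice.

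What is at stake is the power for RTW-SE, the only outcome on which the trial is sized. The number of GPs per practice is settled by recruitment and is hard to change after allocation.

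**Working it through.** **Inputs from the Sample size section.** SD 1.14; difference 0.5 SD = 0.57 points; alpha 0.05; power 80%; 30 analysed patients per GP; ICC 0.15; 12 GPs per arm. Sidedness is not stated. Two-sided is assumed, and it reproduces the stated figure.

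**Step 1: the plan's own figure.**
- Patients per arm without clustering: 2 × (1.96 + 0.84)² / 0.5² = 62.8, so 63.
- Design effect with the GP as cluster: 1 + (30 − 1) × 0.15 = 5.35.
- GPs per arm: 63 × 5.35 / 30 = 11.2, rounded up to 12.
- Recruitment per GP: 30 / (1 − 0.25) = 40.

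All figures agree with the article. At 12 GPs per arm the effective sample size is 360 / 5.35 = 67.3 per arm. Power is 82.6% by the normal approximation and 79.2% by a t test with 22 df. The calculation is therefore correct if every practice supplies one GP.

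**Step 2: two GPs in every practice.** Let ρ be the correlation between patients of different GPs in the same practice. The documents do not give it, so a range is shown. The correlation within one GP stays at 0.15.

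For g GPs per practice, the design effect is 1 + 29 × 0.15 + 30 × (g − 1) × ρ. With g = 2 this is 5.35 + 30ρ. There are 6 practices and 360 analysed patients per arm, and the effective sample size is 360 divided by the design effect. The t column uses 2 × 6 − 2 = 10 df.

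| ρ (assumed) | Design effect | Effective n per arm | Power, normal | Power, t (10 df) |
|---|---|---|---|---|
| 0 | 5.35 | 67.3 | 82.6% | 74.4% |
| 0.01 | 5.65 | 63.7 | 80.6% | 72.1% |
| 0.03 | 6.25 | 57.6 | 76.5% | 67.7% |
| 0.05 | 6.85 | 52.6 | 72.7% | 63.8% |
| 0.075 | 7.60 | 47.4 | 68.2% | 59.4% |
| 0.15 | 9.85 | 36.5 | 57.0% | 48.9% |

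The last row is the case in which 0.15 applies to the whole practice: 1 + 59 × 0.15 = 9.85. The difference detectable with 80% power is then 2.80 × √(2 × 9.85 / 360) = 0.66 SD instead of 0.5.

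**Step 3: break-even.** For 80% (normal), the design effect may be at most 360 / 62.8 = 5.73. With two GPs in every practice, ρ may therefore be at most (5.73 − 5.35) / 30, about 0.013.

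**Step 4: only some practices with two GPs** (12 GPs per arm, normal approximation; the range runs from patient-weighted to optimally weighted analysis).

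| Two-GP practices per arm | ρ = 0.05 | ρ = 0.075 | ρ = 0.15 |
|---|---|---|---|
| 1 | 80.9 to 81.2% | 80.1 to 80.7% | 77.5 to 79.6% |
| 3 | 77.5 to 78.1% | 75.1 to 76.3% | 68.2 to 72.2% |

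**Step 5: restoring 80%** with two GPs per practice and 0.15 at practice level: 63 × 9.85 / 60 = 10.3, so 11 practices or 22 GPs per arm.

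**The case against.** The best defence is that the loss is unknown and may be small. Rounding 11.2 up to 12 leaves some slack. The 57% figure needs two GPs in every practice and the whole ICC lying between practices. The Discussion expects GPs to differ widely in how they handle work problems, because no standard approach exists. That suggests that part of the clustering belongs to the individual GP, so ρ would be below 0.15. This stands, and it is why a range is shown. It does not remove the mismatch: at ρ = 0.05, two-GP practices throughout still give only 73%.

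A reader might infer more than the documents support:

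- **That a single practice with two GPs defeats the 80%.** On the normal approximation it does not. One two-GP practice per arm keeps 80% up to ρ of about 0.075.
- **That the analysis will have an inflated type I error.** This would follow only if the model clustered on GP and left practice out. The Effect evaluation section specifies a multilevel model without naming its levels, which an article may leave to the full plan.
- **That the Effect evaluation section contradicts practice randomisation**, because "patients will be regarded as belonging to the intervention group if their GP was allocated to the intervention condition". This is ordinary intention-to-treat wording: a GP in an allocated practice is allocated.
- **That blocks of two practices endanger the 12 GPs per arm.** A 14/10 split of 24 GPs raises the variance by a factor of (1/14 + 1/10) / (2/12) = 1.029 and lowers power from 82.6% to about 81.6%. That is immaterial.

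**Conclusion.** The concern holds as a mismatch of units. The practice is randomised, while the sample size is valid for independently randomised GPs and allows nothing for correlation between GPs of one practice. On the normal approximation, 80% is assured only if practices contribute essentially one GP each or ρ is negligible (below about 0.013 if every practice supplies two).

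With two GPs in every practice, power ranges from 83% to 57% (normal), or from 74% to 49% (t, 10 df), as ρ goes from 0 to 0.15. The t figures are lower even at ρ = 0, because 12 practices are randomised rather than 24. The number of GPs per practice and ρ are both assumptions. The documents show that the risk is not addressed; they do not show how large it is.

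**What to change.** Restate the sample size with the practice as the cluster. Give the expected number of practices and GPs per practice, say whether the ICC of 0.15 applies to GPs or to practices, state what is assumed for correlation between GPs of one practice, and report the resulting power or detectable difference. Alternatively, admit one participating GP per practice, so that the present figure holds. In either case, name practice, as the randomised unit, as a level in the multilevel model.

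The cost is a revised paragraph and a stated power that will probably be less favourable. Restating needs no extra patients. Restoring 80% might: with two-GP practices and 0.15 at practice level, about 22 GPs per arm would be needed instead of 12. Limiting practices to one GP avoids that, but it requires 24 separate practices.
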